## OUTLINE

### INCLUSION CRITERIA

#### Inclusion criteria

- 13-17 years,
- Primary PTSD diagnosis
- Fluent in Swedish
- Access to the Internet at home or can use vouchers for internet-access to their phone.
- Parent/guardian willing and able to take part in treatment.

#### Exclusion criteria:

##### PTSD is not the primary concern

- Initiation or adjustment of any psychotropic medication within the last 4 weeks prior to commencement of treatment

- Serious mental health symptoms, such as mania, psychosis, alcohol, or substance use disorders or current suicide risk warranting immediate clinical attention.

- Ongoing trauma-focused CBT or Eye movement desensitization and reprocessing Therapy

- Ongoing trauma-related threat

### QUALITY CONTROL

The trial will follow Good Clinical Practice (GCP).

### INTERVENTION

The iTF-CBT protocol mirrors the exact content of first-line treatment for children with PTSD but is delivered through a digital platform and will comprise of text-based material as well as audio files and video illustrations in an age-appropriate manner that the participant gains access to sequentially. iTF-CBT will be therapist-assisted, and each participant will have a designated therapist to guide them through treatment. Treatment will span over 12 weeks and integrates cognitive, behavioral, interpersonal, and family therapy principles as well as trauma interventions. Parallel to the child's treatment, the caregivers are provided the same components and parenting practices, and joint child-parent activities are included.

### COMPARATOR

The active control will consist of therapist-supported internet-delivered psychoeducation and support for the same amount of time. The idea behind this intervention is to control for general non-specific factors (i.e., placebo effects) and at the same time does not exaggerate apparent efficacy of iTF-CBT which may be the case if using a wait-list control condition.

## SAMPLE SIZE

## OUTCOME MEASURES

The power analysis for the RCT is based on the gold-standard interview CAPS-5 where a clinically significant difference in treatment effects is 10 points, which is the between groups difference we aim to detect. With a standard deviation of the CAPS-5 to be 20, this represents a standardized mean difference in terms of Cohens  $d$  of 0.5 and to use it conservatively we used Cohens  $d$  0.4 in our calculations. The estimated number needed is then  $N=240$  (moderate between-group effect size against active control condition at 1-month post-treatment; 95% power, 10% data attrition rate, and an  $\alpha$  level of 0.04). All analysis will be conducted according to the intent to treat principle and we will follow the CONSORT guidelines in reporting and analyzing the data.

The primary hypothesis (clinician-rated CAPS-5-CA) will be evaluated using a linear mixed-effects model with fixed effects of time and group, their interaction, as well as random intercept and slope. Treatment response will be defined as at least 6 points improvement on the CAPS-5 between baseline and participants' last available measurement between baseline and 12-month follow-up (adapted from Schnurr & Lunney, 2016). Secondary self-rated outcomes will be estimated using linear mixed-effects models with repeated measurements and fixed effects of time and group, their interaction, as well as a random intercept and slope.

We will follow the Consolidated Health Economic Evaluation Reporting Standards (CHEERS) guidelines to report the health economic evaluation and look at both direct costs (e.g., therapist time per patient) and other societal costs (e.g., absence from school, caregivers' absence from work). Cost differences between iTF-CBT and the active control condition will be calculated, as well as the incremental cost-effectiveness ratio (ICER). The ICER is a global estimate of cost-effectiveness and represents the additional cost that is associated with the additional clinical effect in one intervention compared with another. Intra-Class Correlations will be used to calculate Interrater agreement on the CAPS-5-CA.

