## DESCRIPTION OF THE STUDY

This study is a single-blind, parallel-group superiority trial with an internal pilot. Study participants will be randomly assigned to 12 weeks of either iTF-CT or therapist-supported internet-delivered psychoeducation on a 1:1 ratio without restriction. To prevent potential selection bias related to the randomization procedure, we will use an external party, the Karolinska Trial Alliance (KTA, [www.karolinskatrialliance.se](http://www.karolinskatrialliance.se)) for that. Allocation concealment will be ensured through randomization after the decision to include each participant has been made. Evaluation includes efficacy, cost-effectiveness, and long-term effects. Outcome measures will be evaluated at baseline, post-treatment, 1-months (primary endpoint), and 6- and 12-months follow-up by assessors blinded to treatment allocation. To ensure blinding integrity, participants and their guardians will receive explicit instructions not to disclose which treatment they have received. After completing the assessment, the blind raters guess the participant's group allocation. If participants inadvertently disclose the treatment allocation during the assessment, another blind assessor will re-assess the diagnosis based on recordings of the clinical interviews. Participants will be recruited nationally through self- or clinician referral. Self-referral will be made available through a dedicated secure website.

The first 20 included participants will not be randomized but will be part of an internal pilot. They will be asked to participate in process evaluation interviews after treatment completion. Interviews will also be conducted with therapists and clinicians recruiting to the study and providing treatment. The aim of this is to see that the recruitment and treatment procedures are feasible and acceptable and that retention to the trial are sufficient to allow the trial to progress.

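### The stated inputs (d = 0.4, 95% power, alpha 0.04, 10% attrition) do not give N = 240, and 240 randomised gives well under 95% power at d = 0.4

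*Protocol*

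**What the plan says.** Protocol, Sample size / Outcome measures. The paragraph starts from the CAPS-5: "a clinically significant difference in treatment effects is 10 points, which is the between groups difference we aim to detect". It continues: "With a standard deviation of the CAPS-5 to be 20", which it converts to d = 0.5. It then lowers the effect, "and to use it conservatively we used Cohens" d of 0.4, and gives N = 240 as the number that follows, with these conditions: "moderate between-group effect size against active control condition at 1-month post-treatment; 95% power, 10% data attrition rate", and an alpha of 0.04. Sidedness is not stated. No baseline to follow-up correlation or other variance reduction is given, although the primary analysis is to be a linear mixed model with random intercept and slope.

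Protocol, Description of the study. The design is a "single-blind, parallel-group superiority trial with an internal pilot" with 1:1 allocation. The first 20 included participants form the pilot and are not randomised.

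Protocol, Objective. The RCT is given as N = 140.

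**The concern.** Every input except sidedness is stated, so the sample size can be checked, and 240 looks too small for 95% power at d = 0.4. The paragraph is the only justification for the size of the primary comparison. If it is wrong, a reader will credit the trial with a 5% false-negative risk at d = 0.4 when the risk is several times that. The reader will also believe that a safety margin below the 10-point target was built in.

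**Working it through.** **Inputs.** From the sample size paragraph: d = 0.4 (reduced from 10/20 = 0.5), power 95%, alpha 0.04, attrition 10%, N = 240. From Description of the study: 1:1 allocation. Assumed: an unadjusted comparison of two means. Sidedness is tried both ways.

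**Step 1: try to reproduce 240.** Per-arm size is n = 2(z_alpha + z_power)² / d².

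- Two-sided: 2(2.054 + 1.645)² / 0.16 = 171 per arm, 342 evaluable, 342/0.9 = 380 randomised. The noncentral t gives 173 per arm, 346 evaluable, 346/0.9 ≈ 385.
- One-sided: 2(1.751 + 1.645)² / 0.16 = 144.1, so 145 per arm, 290 evaluable, 290/0.9 ≈ 322 randomised. The noncentral t also gives 145.
- If 0.04 is a slip for 0.05: 326 evaluable two-sided or 272 one-sided, both before attrition.

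None of these is 240, even with attrition ignored.

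**Step 2: power that 240 delivers.** 240 × 0.9 = 216 evaluable, or 108 per arm. Power ≈ Φ(d√(n/2) − z_alpha), with √(108/2) = √54 = 7.348.

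- d = 0.4, two-sided 0.04: Φ(2.939 − 2.054) = 81.2% (noncentral t 80.8%).
- d = 0.4, one-sided 0.04: Φ(2.939 − 1.751) = 88.3% (t 88.1%).
- d = 0.4, alpha 0.05: 83.3% two-sided, 90.1% one-sided (t).
- d = 0.4, alpha 0.04, no attrition (120 per arm): 84.9% two-sided, 91.0% one-sided (t).
- d = 0.5, two-sided 0.04: Φ(3.674 − 2.054) = 94.7% (t 94.5%).

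**Step 3: which inputs fit 240?** Several sets do:

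- d = 0.5, 95% power, two-sided 0.04, 10% attrition: 220 to 222 evaluable, 245 to 247 randomised (close, not exact).
- d = 0.4, 90% power, one-sided 0.05, 10% attrition: 216 evaluable, exactly 240.
- d = 0.4, 85% power, two-sided 0.04, no attrition: 120 per arm by the normal approximation, exactly 240.

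Each departs from the stated set in at least one input.

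**Step 4: the randomised number is itself unsettled.** If the 20 pilot participants count within 240, then 240 − 20 = 220 are randomised. The Objective gives 140. Power at two-sided alpha 0.04 with 10% attrition (noncentral t):

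| Randomised | Evaluable per arm | d = 0.4 | d = 0.5 |
|---|---|---|---|
| 240 | 108 | 81% | 95% |
| 220 | 99 | 77% | 93% |
| 140 | 63 | 57% | 77% |

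**The case against.** The strongest reply is that the primary analysis is a mixed model that uses baseline, which can be more precise than a comparison of two means. That is true in principle. To reach 95% at d = 0.4 with 108 per arm, two-sided alpha 0.04, the variance factor must fall to 108/171 = 0.632. With a factor of 1 − ρ² (baseline as covariate), that needs ρ ≈ √(1 − 0.632) = 0.61. With a factor of 2(1 − ρ) (a change contrast), it needs ρ ≈ 1 − 0.632/2 = 0.68, and at ρ = 0.5 nothing is gained (81%). Neither factor is exactly the planned model, and the later CAPS-5-CA visits are left out of both. The paragraph states no correlation and derives d from a raw SD of 20. The route is open to the sponsor, but the document does not take it.

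A second reply is that the trial is still well powered for its named target. This stands: if 240 are randomised, power at 10 points and SD 20 is about 95%. A reader might infer that the trial is underpowered for the difference it calls clinically significant; at 240 it is not. What is missing is the margin below that difference.

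Three other inferences go further than the text allows:

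- **That 240 was really computed at d = 0.5.** This is plausible, but at least two other input sets fit exactly.
- **That 0.01 of alpha has gone astray.** A protocol may choose 0.04, and no alpha split is described. Confirming the value is enough.
- **That the trial was sized for 8 points.** The paragraph never says 8. That figure holds only if SD stays at 20; 10 points with SD 25 also gives 0.4.

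**Conclusion.** The paragraph is wrong as written. For an unadjusted comparison, no reading of sidedness, attrition or a slip in alpha makes 240 sufficient for 95% power at d = 0.4. With 240 randomised and 10% attrition at alpha 0.04, the false-negative risk at d = 0.4 is about 19% two-sided or 12% one-sided, against the stated 5%. The 81% figure is therefore conditional on a two-sided test and on 240 actually being randomised. The finding concerns the stated power and the claimed caution; it does not show that more participants are needed. The origin of 240 remains unknown.

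**What to change.** 1. Reconcile the randomised number: 140 in the Objective, 240 in the sample size paragraph, and whether the 20 non-randomised pilot participants count within it.
2. State one alpha and its sidedness, and use the same for the primary test.
3. Replace the power claim with what that number delivers. For 240, for example: *With 240 randomised and 10% attrition (216 evaluable), two-sided alpha 0.04, power in an unadjusted comparison is about 81% for d = 0.4 (8 points if the SD is 20) and about 95% for d = 0.5 (10 points).* For 220 randomised the figures are about 77% and 93%; for 140, about 57% and 77%. If alpha is two-sided 0.05, 240 gives about 83% at d = 0.4.
4. Delete the claim of 95% power at d = 0.4, unless a gain from the mixed model is claimed. In that case state the assumed baseline to 1-month correlation and the formula used.

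The cost is a rewritten paragraph and a consistent N across sections. No extra enrolment follows from this point, but the power reported at d = 0.4 becomes less favourable.

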### Research questions:

1. Is guided iTFCBT more efficacious than an active control condition (therapist-supported internet-delivered psychoeducation and support) in regard to reduction of blinded assessor rated PTSD symptom severity 1-month post-treatment?
2. Is guided iTFCBT more cost-effective than an active control condition (therapist-supported internet-delivered psychoeducation and support) in regard to reduction of blinded assessor rated PTSD symptom severity 1-month post-treatment?

3. Are the therapeutic gains of iTF-CBT maintained at long term follow up (6 and 12 months after treatment)?
4. How do children, parents and therapists perceive iTF-CBT?

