## ASSESSMENT POINTS

The primary outcome measure, CAPS-5 CA, will be conducted at baseline, 1-month post-treatment (primary endpoint), and at 6-month and 12-month follow-ups (secondary endpoints). Self-administered measures will be used at baseline, post-treatment, 1-month post-treatment (primary endpoint), and at 6-month and 12-month follow-ups. Self-administered measures of PTSD (CATS-2) and adverse events are also administered weekly through the treatment period.

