## OUTCOME MEASURES

- Clinician Administered PTSD Scale Children and Adolescent version 5 (CAPS-5-CA), the gold standard clinical interview to assess PTSD symptom severity and diagnosis of PTSD [42] at baseline and the 1-month, 6-months and 12-months follow up.
- The Child and Adolescent Trauma Screen (CATS-2) at baseline, weekly through the treatment period, post-treatment and at the 1-month, 6-month and 12-month follow up.
- Mood and Feelings Questionnaire (MFQ) at baseline, post-treatment and at the 1-month, 6-month and 12-month follow up.

- The Education, Work and Social Adjustment Scale, Youth and Parent (EWSAS) at baseline, post-treatment and at the 1-month, 6-month and 12-month follow up.
- Treatment Inventory of Costs in Psychiatric Patients (TIC-P) at baseline, post-treatment and at the 1-month, 6-month and 12-month follow up.
- The Negative Effects Questionnaire (NEQ) at post-treatment and at the 1-month, 6-month and 12-month follow up.
- Assessment of Quality of Life KIDSCREEN at baseline, post-treatment and at the 1-month, 6-month and 12-month follow up.
- The Client Satisfaction Questionnaire (CSQ-8) at post-treatment.
- The Working Alliance Inventory (WAI) after completion of treatment module 3.
- The Credibility/Expectancy Questionnaire (CEQ) after completion of treatment module 1.

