## TIME PLAN

Participants will be recruited and provided treatment starting winter 2023. Statistical analyses will be done immediately after the last participant has completed the post-

assessment. First publication is estimated to late 2024 or beginning of 2025. All data will be handled and eventually archived according to Swedish and European legislation.

2023 Q3-Q4: Develop the iTF-CBT treatment and set up the platform.

2024: Q1 Commencement of the RCT with an internal pilot study and follow-up assessments. Refinement of treatment.

2024 Q2-Q4: Completion of treatments and 6 months follow-up assessments. Analysis of results, manuscript draft of pilot part of RCT.

2026 Q4: Completion of 12 months follow-up assessments.

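### The stated primary model is not tied to the 1-month primary endpoint, and its random slope needs visits after that endpoint

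*Protocol*

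**What the plan says.** The endpoint is fixed at one visit. The first research question asks about efficacy "in regard to reduction of blinded assessor rated PTSD symptom severity 1-month post-treatment". Assessment Points says that CAPS-5-CA "will be conducted at baseline, 1-month post-treatment (primary endpoint), and at 6-month and 12-month follow-ups (secondary endpoints", and the later Outcome Measures list gives the same visits: "at baseline and the 1-month, 6-months and 12-months follow up". The power calculation, in the text under Sample Size / Outcome Measures, concerns the same visit: "a clinically significant difference in treatment effects is 10 points, which is the between groups difference we aim to detect". It then takes the more cautious d = 0.4, which is 8 points at the stated SD of 20.

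The next paragraph of that section sets the analysis. The primary hypothesis "will be evaluated using a linear mixed-effects model with fixed effects of time and group, their interaction, as well as random intercept and slope". The protocol does not say whether time is numeric or categorical, which visits enter the model, or which term is the primary test.

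Two other places leave the visits unsettled. Description of the Study adds a post-treatment assessment: "Outcome measures will be evaluated at baseline, post-treatment, 1-months (primary endpoint), and 6- and 12-months follow-up by assessors blinded to treatment allocation". Time Plan says "Statistical analyses will be done immediately after the last participant has completed the post"-assessment, when later follow-up would be incomplete.

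**The concern.** The endpoint and the sample size concern a difference at one visit. The model is written as a growth model. A random slope is a slope on numeric time, and the natural companion is a linear fixed effect of time, so the group-by-time term would be a difference in straight-line slopes across all CAPS-5-CA visits.

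A gain during treatment ("Treatment will span over 12 weeks") followed by a plateau is not a straight line. The slope test would then answer a different question from the primary one. It would depend heavily on the 6- and 12-month data, which the protocol calls secondary. The maintenance question (the third research question) would suffer too, because one slope cannot separate the gain during treatment from what happens afterwards.

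**Working it through.** **Can the stated model be fitted to baseline and 1 month alone?** Put the two visits at times 0 and t. With intercept variance a, slope variance b, intercept-slope covariance c and residual variance s:

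- Var(baseline) = a + s
- Cov(baseline, 1 month) = a + tc
- Var(1 month) = a + 2tc + t²b + s

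There are three observable quantities and four unknowns. The components are not identified unless a restriction such as c = 0 is added, and the protocol states none. With all four visits there are 4 × 5 / 2 = 10 variances and covariances, and the model can be fitted. As written, it therefore needs visits after the primary endpoint.

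**Inputs from the protocol.** SD 20; difference 8 points (0.4 × 20); alpha 0.04, sidedness not stated and taken as two-sided (critical value 2.054); N = 240 less 10% attrition, so 240 × 0.9 / 2 = 108 per arm.

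**Assumptions not in the protocol.** Within-person correlation 0.5; linear time; visits at 0, 4, 9 and 15 months from baseline (12 weeks is about 2.8 months, so the visits fall at about 3.8, 8.8 and 14.8, rounded). Differences are signed so that a positive value favours iTF-CBT.

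**The plan's own figure.** For one difference at one visit, n per arm = 2 × [(2.054 + 1.645) / 0.4]² = 171, that is 342 evaluable and 342 / 0.9 = 380 in total. The stated 240 does not reproduce. At 108 per arm, power for d = 0.4 is Φ(0.4 × √54 − 2.054) = Φ(0.885) = 81%. That discrepancy, and the N = 140 under Primary Objective, are separate matters. The 108 per arm serves here only as a common base.

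**Linear slope, true differences 0, 8, 8, 8.** With balanced data a random intercept and slope model returns the ordinary least-squares slope.

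- Mean time 7; Sxx = 49 + 9 + 4 + 64 = 126
- Slope = (−3×8 + 2×8 + 8×8) / 126 = 56 / 126 = 0.444 points per month
- Fitted baseline difference = 6 − 7 × 0.444 = 2.89, where the truth is 0
- Fitted change by 1 month = 4 × 0.444 = 1.78; fitted difference at 1 month = 2.89 + 1.78 = 4.67, where the truth is 8
- SE of slope = √[2 × 400 × 0.5 / (126 × 108)] = 0.171; z = 2.59; power = Φ(2.59 − 2.054) = 70%

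**1-month contrast, same inputs.**

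- Unadjusted change from baseline: SE = √(2 × 400 / 108) = 2.72; z = 2.94; power 81%
- Adjusted for baseline: SE = √(2 × 400 × 0.75 / 108) = 2.36; z = 3.39; power 91%

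**Other trajectories, slope test.**

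| True differences at 0, 1, 6, 12 months | Slope per month | z | Slope test significant |
|---|---|---|---|
| 0, 8, 6, 2 (groups converge) | 4/126 = 0.032 | 0.19 | about 4% |
| 0, 0, 4, 8 (groups diverge only later) | 72/126 = 0.571 | 3.33 | about 90% |

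**Sensitivity.** The SE above sets the random-slope variance to zero. With a random-slope SD of 8 points over the full span, the three slope powers become 63%, 4% and 85%. With unrounded visit times, that slope variance and an intercept share of 0.3 to 0.7 of the variance:

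- differences of 8, 8, 8 after baseline: 49 to 80% for the slope, 66 to 96% for the unadjusted 1-month contrast
- 8, 6, 4: 9 to 15% against 66 to 96%
- 0, 6, 8: the slope test rejects in 77 to 97% of trials although there is no 1-month effect

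**The case against.** The strongest reply is that the protocol never says time is linear, never says that 12-month data enter the primary test, and never names the interaction slope as that test. Time coding, visits and the named contrast are often left to a statistical analysis plan, which is not shown here.

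Much of this stands. A reader might infer that the primary test is a trajectory to 12 months, or that no reading of the model tests the 1-month effect. The protocol supports neither. With categorical fixed time, the group-by-1-month coefficient is exactly the single-df difference in change, and it can sit beside a random slope on numeric time. With baseline and 1 month only, the group-by-time effect is also the right quantity: the failure of identification concerns only how the variance is split, and dropping the redundant random term cures it. A reader might also infer that the weekly CATS-2 scores enter the same model. The protocol sets a similar model for secondary self-rated outcomes but does not say that the weekly scores are used.

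The figures need care as well. About half of the gap between 70% and 91% comes from baseline adjustment; the like-for-like comparison is 70% against 81%. The 1.8 points leave out the fitted baseline gap, so 4.7 is the fitted 1-month difference. The converging and diverging patterns are chosen illustrations.

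The reply does not remove the point. The protocol does not stay silent on the model: it commits to a random slope, and that commitment needs visits beyond the endpoint. An analysis plan that follows it literally would inherit the mismatch.

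**Conclusion.** The concern holds in this form: the stated primary model is not tied to the 1-month endpoint, and its random slope (with intercept and slope free to correlate) needs the later visits. The identification argument rests on the visit schedule in Assessment Points and the Outcome Measures list. A post-treatment CAPS-5-CA, as Description of the Study could suggest, would supply a third visit up to 1 month.

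The size is conditional on the linear-time reading, the assumed visit times and correlation, and the assumed trajectory. For a difference that is constant from 1 month, an 8-point effect is fitted as about 4.7 points, and power falls by about 11 percentage points like for like, or 21 against a baseline-adjusted contrast. Convergence or late divergence does more harm: the slope test can miss a real 1-month effect or be significant without one. Under a categorical-time reading with the 1-month contrast as the test, the loss disappears.

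**What to change.** Replace the model sentence in the protocol with a repeated-measures mixed model that has:

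- categorical time (baseline, 1, 6 and 12 months) and group-by-time;
- baseline CAPS-5-CA constrained equal across arms or used as a covariate (in which case only the later visits are outcomes);
- an unstructured within-person covariance in place of the random intercept and slope;
- the single-df between-group contrast at 1 month, named as the primary test.

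Answer the maintenance question by the 6-versus-1 and 12-versus-1-month contrasts from the same model. State which visits enter the primary analysis, and reconcile the post-treatment assessment in Description of the Study and the analysis date in Time Plan with that choice.

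The cost is protocol wording and a few more covariance parameters: 10 for four visits, against 4 in the stated model. No new data are needed. The change should be made before any unblinded analysis, since it settles which test decides the trial.

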Consecutive applicants referred to the study are assessed for eligibility. Interested applicants are screened on the telephone after completion of screening measures for PTSD, and eligible youths and their families are invited to a psychiatric assessment via video-conferencing or face-to-face. The aim of this visit is ensuring eligibility by verification that PTSD is the primary diagnosis and other inclusion/exclusion criteria, assess severity of PTSD symptoms, and assess for comorbidity. The gold standard clinical interview CAPS-5-CA that assesses past month diagnosis of PTSD and PTSD symptom severity will be used to ensure validity and reliability of the PTSD diagnosis. The interview will also include the child version of the Mini International Neuropsychiatric Interview (MINI-KID). The assessor also provides detailed information about the study and treatment including objectives, benefits, risks, and requirements imposed by the study during this visit. The information is also provided in writing. If the applicant is eligible for the study, the study participant and guardian sign informed consent digitally during this visit.

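### The primary model does not adjust for the CAPS-5-CA score taken before randomisation: it is valid, but it forgoes precision, and the amount depends on inputs the protocol does not give

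*Protocol*

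**What the plan says.** Under Sample size / Outcome measures, the protocol evaluates the primary hypothesis with a "linear mixed-effects model with fixed effects of time and group, their interaction, as well as random intercept and slope". No baseline covariate and no constraint of equal baseline means is stated there or elsewhere. Time coding and the tested contrast are not given.

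Under Assessment points: "The primary outcome measure, CAPS-5 CA, will be conducted at baseline, 1-month post-treatment (primary endpoint), and at 6-month and 12-month follow-ups (secondary endpoints". The first research question is framed "in regard to reduction of blinded assessor rated PTSD symptom severity 1-month post-treatment".

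The baseline rating precedes allocation. Description of the study and Inclusion procedure both place CAPS-5-CA at the eligibility visit, where it "will be used to ensure validity and reliability of the PTSD diagnosis". Description of the study then says: "Allocation concealment will be ensured through randomization after the decision to include each participant has been made". Allocation is 1:1 without restriction, so no stratification on severity is stated.

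The power calculation is a plain two-group one. It states that "a clinically significant difference in treatment effects is 10 points", and "With a standard deviation of the CAPS-5 to be 20". It uses d = 0.4 to be conservative, with 95% power, 10% attrition, alpha 0.04 and N=240. It gives no correlation between baseline and follow-up.

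**The concern.** Because the baseline score is taken before allocation, any baseline difference between the arms is chance. With baseline among the modelled time points, which is the natural reading, the free group main effect makes the model estimate that difference as if it could be real. The group-by-time contrast then subtracts the whole of it, although only a fraction rho is expected to carry over to follow-up when the SDs are equal.

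What is at stake is precision. The standard error of the primary contrast is larger than the data require, and in any one trial a chance baseline imbalance moves the estimate in the opposite direction. The information that would prevent this is already collected.

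**Working it through.** **Inputs.** From Sample size / Outcome measures: d = 0.4, SD = 20 (so 0.4 × 20 = 8 points), alpha 0.04 (sidedness not stated; two-sided assumed), 95% power, 10% attrition, N = 240. Evaluable per arm: 240 × 0.9 / 2 = 108. Assumed, because the protocol does not give them: the baseline-to-1-month correlation rho (range 0.3 to 0.7), and k, the ratio of baseline SD to follow-up SD (1 unless stated).

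**The plan's own figure.** n per arm = 2(2.054 + 1.645)² / 0.4² = 171, so 342 evaluable and 342 / 0.9 = 380 to randomise. N=240 is not reproduced. With 108 per arm, a plain two-group comparison at d = 0.4 has 80.8% power (noncentral t).

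**Variance factors**, relative to the follow-up variance, for the 1-month contrast with categorical time and complete data:
- model as stated (difference in change): 1 + k² − 2·rho·k, which is 2(1 − rho) at k = 1
- baseline-adjusted: 1 − rho²
- difference between the two: (k − rho)², never negative and zero only when k = rho

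At rho 0.5 and k = 1 the factors are 1.00 and 0.75. The SE falls from 20·√(2/108) = 2.72 points to 2.72·√0.75 = 2.36 points. A generalised least squares check on four visits with exchangeable correlation 0.5 gives the same two factors, for a free group effect and a common baseline mean respectively.

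**Power** (noncentral t, effective d = 0.4 / √factor, 108 per arm, k = 1):

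| rho | 1-month score only | model as stated | baseline-adjusted | gain over stated model (points) |
|---|---|---|---|---|
| 0.3 | 80.8% | 66.2% | 84.4% | 18.2 |
| 0.5 | 80.8% | 80.8% | 90.7% | 9.9 |
| 0.6 | 80.8% | 88.8% | 94.5% | 5.7 |
| 0.7 | 80.8% | 95.7% | 97.9% | 2.2 |

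**Sensitivity at rho 0.5:**
- k = 0.9: factor 0.91, 84.4% to 90.7%, gain about 6 points
- k = 0.8: factor 0.84, 87.2% to 90.7%, gain about 3.5 points
- k = 0.7: factor 0.79, 89.2% to 90.7%, gain about 1.5 points
- N = 380, k = 1: 94.9% to 98.6%, gain 3.7 points
- N = 240, d = 0.5, k = 1: 94.5% to 98.5%, gain 4.0 points
- N = 140 (the figure under Objective), k = 1: 56.8% to 69.7%, gain 12.9 points

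**Chance imbalance.** With 120 randomised per arm, the SE of the baseline difference is 20·√(2/120) = 2.6 points. At rho 0.5, an imbalance of that size shifts the change-score estimate by (1 − 0.5) × 2.6 = 1.3 points relative to the adjusted one, about 16% of 8 points.

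**Numeric time.** The interaction is then a slope difference over all visits, and the factors above do not apply. I compared the variance of the slope difference with and without a free group term, under a random intercept and slope. The assumed components were intercept SD 14, residual SD 14 and slope SD 2 per time unit, which give rho of about 0.5:
- visits at 0, 4, 9 and 15 months, intercept-slope correlation +0.3: variance cut below 1%
- visits coded 0, 1, 2, 3, correlation −0.3: variance cut about 31%

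**The case against.** **The model is conventional and valid.** This is true and it stands. Under randomisation the contrast is unbiased and keeps its type I error, and it addresses the reduction that the research question asks about. A reader might infer from the imbalance argument that the primary estimate is biased. The documents do not support that: randomisation balances baseline in expectation, and the shift is conditional on a chance imbalance.

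**Covariates can be left to a statistical analysis plan.** Often so, and time coding and the named contrast may well be settled there. But this protocol lists the fixed effects of its primary model, and baseline adjustment is not among them. If baseline were instead left out of the response, the test would be an unadjusted comparison of follow-up scores, and adjustment would still help (80.8% to 90.7% at rho 0.5).

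**The trial is not losing power against its plan.** A reader might take the 10 points as a loss against what was planned. The plan's calculation uses no baseline information. At rho 0.5 with equal SDs the stated model has exactly the power of that calculation. Above 0.5 it has more; it has less only below 0.5 (66.2% against 80.8% at 0.3). No correlation is given, so the documents do not show a shortfall.

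**The gain looks large because N=240 is too small for the stated inputs, and it rests on two unknowns.** Both parts stand. At N=380, or at the 10-point difference (d = 0.5), it is about 4 points. Entry requires a PTSD diagnosis, so the baseline SD may well be the smaller one, which reduces the gain.

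**A random slope suggests numeric time.** It does. The direction of the point survives, but the power figures do not carry over.

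**Conclusion.** The point holds as a matter of efficiency. For a categorical 1-month contrast with equal SDs and the protocol's N, d, alpha and attrition, baseline adjustment adds about 18 points of power at rho 0.3, 10 at rho 0.5 and 2 at rho 0.7. It is never less efficient in large samples. Both rho and the SD ratio are assumptions: at rho 0.5 the gain falls to about 6, 3.5 and 1.5 points at SD ratios of 0.9, 0.8 and 0.7. If time is numeric, only a variance reduction can be stated, from near 0 to about 30% depending on variance components and visit coding.

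A reader might also infer that adjustment would restore the stated 95% power. It would not: at rho 0.5 the requirement is 171 × 0.75 = 128.2, so 129 per arm, 258 evaluable and 258 / 0.9 = 287 randomised. The mismatch between N=240 and 95% power, and between 240 and the 140 under Objective, must be resolved separately.

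The change is worth making because it is nearly free, not because the stated analysis is wrong.

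**What to change.** Under Sample size / Outcome measures, restate the primary model with visit as a categorical factor and one of the following:
- a common baseline CAPS-5-CA mean for both arms, with no group term at baseline and group-by-visit terms after it; or
- baseline CAPS-5-CA as a covariate, with only post-baseline visits as the response.

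Name the baseline-adjusted group difference at 1 month as the primary estimate. The common-baseline form also keeps participants who have only a baseline value.

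Use the same form for the secondary self-rated outcomes, but apply the common-baseline constraint only where the baseline rating precedes allocation. Baseline assessment places those questionnaires before the start of treatment, which does not settle whether they come before randomisation.

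The cost is one sentence in the protocol or the statistical analysis plan, with no new data, visits or participants. It must be fixed before the analysis to count as prespecified.
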